### Sample Size Calculation

First, we calculated the sample size for an individually randomized two-arm study with 80% power and 5% type I error. We estimated the rate of falls for the control group as 120 per 100-person years, consistent with prospective studies documenting fall rates in similar populations of patients with COPD in Canada and Australia [7,10]; the rate of falls in the intervention group was estimated as 84 per 100-person years, which corresponds to a 30% reduction in the rate of falls. A 30% reduction in fall rate is widely used as a clinically significant threshold in fall prevention studies and is consistent with meta-analyses demonstrating the effect of multi-component exercise on fall rate. Based on this data, the estimated number of participants in each arm with 1-year follow up is 124 patients. However, our study is a multicenter study in which participants are clustered within nine centers. Assuming a coefficient of variation of size 0.10, we need, on average, 19 participants in each arm per site, corresponding to a total of 171 participants in each arm, to account for the clustering of the study [58].

Assuming a similar clustering effect for the secondary outcomes with a sample size of 171 participants in each arm and nine centers, our study has 80% power with 5% type I error to detect differences of the following magnitudes (MCID: minimal clinically important difference):

Berg Balance (SD=6.15, MCID=5) differences of 3.0 units or larger.BESTest (SD=13, MCID=13) differences of 6.4 units or larger.ABC (SD=23.2, MCID=19) differences of 11.5 units or larger.Chair stand (SD=4.8, MCID=3) differences of 2.4 units or larger.

These values are close to half the standard deviation of the outcome measures and are sufficient to detect clinically important changes [45].

We anticipate a loss to follow-up of 15%-20% based on previous trials in PR and have inflated our sample size to 400 participants (200 in each arm) to account for this. Should a participant be unable to attend an assessment session at a study center, we will minimize loss to follow-up by offering to complete assessments in the participants’ homes.

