There is growing recognition of an increased fall risk in people with COPD [7-10]. In addition to impaired balance, other fall risk factors in COPD include the use of multiple medications, muscle weakness, cognitive impairment, and comorbidities such as osteoarthritis and osteoporosis [7]. COPD was second only to osteoarthritis in its association with the number of falls in a large cohort study of elderly women [9] and was the only chronic condition that predicted falls in a further cohort study of 16,000 participants [8]. Patients with COPD have reported a higher prevalence of falls (40%-55%) [10,11,15,17] than the general elderly population and in two prospective studies [7,10], the annual fall rate in COPD was up to five times higher than expected based on age alone. Fall-related injuries as well as associated hospitalizations are also common in people with COPD [18,25]. In those with more severe disease and depression, a history of falling is a strong predictor of mortality [19]. These data emphasize the need for the development of fall prevention strategies specific to individuals with COPD.

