### Data Analysis

The data analysts on the research team will be blinded to group allocation. Descriptive summary statistics will be reported using mean, median, and standard deviation for continuous measures, and frequency and counts for categorical variables. For the primary outcome, we will use random effect Poisson (Negative Binomial) regression model to compare the number of falls at 12-month follow-up between intervention and control groups adjusting for potential confounders, repeated measures, and clustering of participants within centers. For secondary outcomes, we will use random effect linear regression to compare intervention and control groups adjusting for potential confounders and clustering of the observations. For all measures, we will perform intention-to-treat and per protocol analysis.

We will estimate the total cost for the intervention and control groups and calculate the difference between the two groups. Similarly, for the effect measures, we will calculate the difference in the number of falls and in the QALY between groups. The summary measure for the economic analysis will be the incremental cost per number of falls averted (cost-effectiveness analysis) and the incremental cost per QALY gained (cost-utility analysis) for the intervention group compared with the control. Given that this economic analysis will be using data primarily from study participants, nonparametric bootstrap will be used to calculate the 95% confidence interval around the incremental ratios. The decision uncertainty will be presented using cost-effectiveness acceptability curves that show the probability of the intervention being cost-effective compared with the control group at a wide range of willingness to pay for a QALY [57].

No interim or subgroup analysis is planned. We will perform both intention-to-treat and per protocol analyses.

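### The 80% power for falls assumes Poisson variance although the planned model allows extra-Poisson variation; with 171 per arm it holds only if dispersion k is at most about 0.37

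*Protocol article*

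**What the plan says.** In the protocol article, the Sample Size Calculation section begins: "we calculated the sample size for an individually randomized two-arm study with 80% power and 5% type I error". It continues "We estimated the rate of falls for the control group as 120 per 100-person years", takes 84 per 100 person-years for the intervention arm (a 30% reduction), and concludes: "Based on this data, the estimated number of participants in each arm with 1-year follow up is 124 patients". It then allows for centres: "Assuming a coefficient of variation of size 0.10, we need, on average, 19 participants in each arm per site", which gives 171 per arm over nine centres. Finally it goes to 200 per arm for an expected loss of 15% to 20%. No dispersion parameter is given at any step.

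The Data Analysis section plans a "random effect Poisson (Negative Binomial) regression model to compare the number of falls at 12-month follow-up" between the groups, adjusted for confounders, repeated measures and clustering within centres. It gives no reason for this choice of model.

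The Introduction supplies one further figure: "Patients with COPD have reported a higher prevalence of falls (40%-55" (the quotation stops inside the printed range of 40% to 55%). No recall period is given.

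**The concern.** The sample size and the primary analysis rest on different variance assumptions. A Poisson calculation treats everyone in an arm as having the same fall rate. A negative binomial model, or a Poisson model with a participant random effect, lets rates differ between people, and that extra variance widens the confidence interval for the rate ratio. If such variation is present, the number that gives 80% power under Poisson gives less under the planned model.

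The prevalence figure is a reason to take this seriously. A Poisson mean of 1.2 falls implies that about 70% of controls fall at least once in the year, well above 40% to 55%.

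At stake is how the primary result is read. The power statement is unqualified, and the trial is meant to inform guidelines. A non-significant result set against a claimed 80% power could be taken as evidence against a 30% reduction when the trial could reliably detect only a larger one.

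**Working it through.** **Inputs from the Sample Size Calculation section:** rates 1.20 and 0.84 per person-year (rate ratio 0.70), one year of follow-up, equal arms, 80% power, 5% type I error, centre coefficient of variation 0.10, nine centres. Sidedness is not stated; two-sided reproduces the printed figure (one-sided gives 98). (1.960 + 0.842)² = 7.849.

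**1. The 124.** With variance equal to the mean: n = 7.849 × (1.20 + 0.84) / 0.36² = 123.5, so 124. Exact match.

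**2. The 171.** The standard formula for comparing rates across clusters, with y participants per arm per centre, is 9 = 1 + 7.849 × [2.04/y + 0.10² × (1.20² + 0.84²)] / 0.36². This gives y = 16.01 / (1.037 − 0.168) = 18.4, so 19 per site and 9 × 19 = 171. The within-centre term, 2.04/y, is still Poisson; only variance between centres has been added.

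**3. The same design with dispersion k** (variance = mean + k × mean²), tested on the log rate ratio:

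- n = 7.849 × (1/1.20 + 1/0.84 + 2k) / (ln 0.70)² = 61.7 × (2.024 + 2k)
- Power at N per arm = Φ(0.3567 / √[(2.024 + 2k)/N] − 1.96)
- Share of controls with at least one fall in a year = 1 − (1 + 1.2k)^(−1/k)

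Break-even at 171: 171/61.7 = 2.772, and (2.772 − 2.024)/2 = 0.37. At k=1: √(4.024/171) = 0.1534, 0.3567/0.1534 − 1.96 = 0.365, power 64%.

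| k | Controls falling in a year | n per arm for 80% | Power at 171 | Power at 200 (no loss) |
|---|---|---|---|---|
| 0 | 70% | 125 | 91% | 94% |
| 0.37 | 63% | 171 | 80% | 86% |
| 0.56 | 60% | 195 | 75% | 81% |
| 0.96 | 55% | 244 | 65% | 72% |
| 1 | 55% | 249 | 64% | 71% |
| 2 | 46% | 372 | 48% | 54% |
| 2.97 | 40% | 492 | 38% | 43% |

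(The log scale gives 125 rather than 124 at k=0; the difference is immaterial.) The power columns credit the whole step from 124 to 171 as room for overdispersion. That is generous to the plan, but reasonable because the Allocation section randomises individuals within site.

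**4. Detectable rate ratio R at 171 per arm.** Solving 7.849 × (1/1.2 + 1/(1.2R) + 2k) / (ln R)² = 171 gives R = 0.70 at k=0.37, about 0.65 at k=1 and about 0.59 at k=2.

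**5. Simulation check.** Negative binomial fits to 500 simulated trials per setting gave 63% power at 171 per arm with k=0.97, 41% at 171 with k=2.5, and 72% at 200 with k=0.97, in line with the formula.

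**6. What k might be.** The document gives none. If the 40% to 55% is a one-year figure for patients with a mean of 1.2 falls, k runs from 2.97 down to 0.96. If it covers six months (mean 0.6), a pure Poisson process already gives 45% fallers, so 45% or more implies essentially no overdispersion, and 40% implies k=0.61 (power 73% at 171). At nine months (mean 0.9), 55% gives k=0.29 and 82% power, while 40% gives k=2.04 and 47%. A window longer than a year implies a larger k and lower power.

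**The case against.** A reader might infer that the protocol's own figures prove a specific shortfall, with power of 38% to 65%. The document does not support that as a settled figure, for three reasons:

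- The rate is attributed to references 7 and 10, and the prevalence to references 10, 11, 15 and 17. Only one source is shared, and no place gives both quantities for the same cohort.
- The recall window is not stated, and step 6 shows how strongly k depends on it.
- The Participants section requires a self-reported decline in balance, a fall in the last 2 years or a recent near fall. The enrolled patients may fall more often than COPD patients in general; at 60% fallers power at 171 is 75%, a modest gap.

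These points stand, and they make the size of the shortfall conditional.

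Two other inferences also fail. The document does not say that the negative binomial was chosen because fall counts are overdispersed. Nor is there an arithmetic error: 124 and 171 both reproduce.

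It can also be said that monthly diaries let people who leave early contribute person-time, and that covariate adjustment may reduce residual dispersion. The first helps a little: if 20% of 200 per arm leave at half a year, power at k=1 is about 68% rather than 64%. The document does not quantify the second. If instead a plain Poisson model were fitted, the problem would not vanish, because overdispersion would then make the standard errors too small.

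None of this supplies the missing dispersion assumption. Nor can it be left to an analysis plan, since the power claim is made here in full and without qualification.

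**Conclusion.** The concern holds as an unsupported variance assumption behind a stated power. Neither the 124 nor the 171 allows for differences in fall risk between people, while the planned primary model does. With rates of 1.20 and 0.84 and 171 evaluable per arm, the 80% is right only for k up to about 0.37, equivalent to about 63% or more of controls falling within a year. These results follow from the stated inputs and the negative binomial formula, without covariate adjustment.

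The range of 38% to 65% power rests on two further assumptions: that the quoted prevalence covers about one year, and that it applies to the enrolled patients. A shorter window or a higher-risk sample makes the shortfall smaller, possibly nil; a longer window makes it larger. What can be said firmly is that 80% is one end of a plausible range and is presented as the only value. No bias or inflated type I error is shown, since a negative binomial model accommodates the extra variation.

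**What to change.** In the Sample Size Calculation section, replace the unqualified 80% with a negative binomial calculation that states the assumed dispersion and its source, and report power and detectable rate ratio over a range of k. For example: with 171 evaluable participants per arm and a control rate of 1.20 per person-year, power for a rate ratio of 0.70 is 80% at k=0.37, 64% at k=1 and 48% at k=2, and the rate ratio detectable with 80% power is 0.70, about 0.65 and about 0.59 respectively. If the prevalence range is used to support a value of k, give its recall period and say whether it applies to patients selected for balance problems or falls.

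This is a change of wording. It needs no extra patients and no change to the analysis model. The cost is a less favourable stated power.

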### Allocation

A computer-generated block randomization table will be created by a member of the research team not involved in recruitment. A randomization schedule will be provided for each site. After an individual has been enrolled in the study and the baseline assessment has been completed, the central research coordinator will consecutively allocate participants using sealed opaque envelopes and advise each site coordinator of group allocation.

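### The increase from 124 to 171 per arm reproduces from a cluster-randomised formula, but individuals are randomised within sites, so the stated 80% power and the secondary detectable differences are wrong as written

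*Protocol article*

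**What the plan says.** The Sample Size Calculation section works in two steps. In the first, "we calculated the sample size for an individually randomized two-arm study with 80% power and 5% type I error", with a control rate of 1.20 and an intervention rate of 0.84 falls per person-year, and the result is that "the estimated number of participants in each arm with 1-year follow up is 124 patients". The second step rests on the observation that "our study is a multicenter study in which participants are clustered within nine centers". "Assuming a coefficient of variation of size 0.10", the authors conclude that "we need, on average, 19 participants in each arm per site, corresponding to a total of 171 participants in each arm". The method is cited to a reference that is not reproduced. The section then assumes a comparable clustering effect for four secondary outcomes, lists their detectable differences, and raises the total to 400 for a loss of 15%-20%.

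On design, the Abstract says that individuals are randomised, and the Allocation section specifies block randomisation: "A randomization schedule will be provided for each site". The Data Analysis section plans a random-effect Poisson (negative binomial) model that accounts for centre.

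**The concern.** A cluster-trial inflation is needed when whole centres are allocated to one arm, because differences between centres then look like differences between treatments. Here each centre supplies both arms. A centre with a high fall rate raises both arms alike, and the ratio between them is unaffected. Multicentre data call for centre in the model, which the plan has, but not for this inflation.

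At stake is what the 80% figure means. A reader will take it that the extra variance in this trial has been allowed for. The allowance is for a component that the design removes, while dispersion between people, which the planned negative binomial model expects, does not enter the calculation. The secondary detectable differences inherit the problem.

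**Working it through.** **Inputs** (Sample Size Calculation): λ0 = 1.20, λ1 = 0.84, power 80%, type I error 5%, nine centres, coefficient of variation k = 0.10. Two-sided testing is assumed: (1.960 + 0.842)² = 7.849. A one-sided test would give 98 per arm, not 124.

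**Step 1: reproduce 124.** n = 7.849 × (λ0 + λ1)/(λ0 − λ1)² = 7.849 × 2.04/0.1296 = 123.5, rounded up to 124. It matches.

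**Step 2: reproduce 171.** The unmatched cluster-randomised formula for rates, with c clusters per arm and y person-years per cluster, is

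c = 1 + 7.849 × [(λ0 + λ1)/y + k²(λ0² + λ1²)]/(λ0 − λ1)².

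With c = 9: 8 × 0.1296/7.849 = 0.1321; subtract 0.01 × (1.44 + 0.7056) = 0.0215 to leave 0.1106; y = 2.04/0.1106 = 18.44, rounded up to 19; 19 × 9 = 171. It matches exactly. Variants do not:

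| Variant | Result |
|---|---|
| Matched (+2 in place of +1) | 22 × 9 = 198 |
| No small-sample term | 17 × 9 = 153 |
| Nine clusters in total | 56.1 per cluster |

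The matching version thus treats the trial as 18 clusters, nine wholly in each arm. The +1 term alone moves 123.5 to 139.0, k = 0.10 takes it to 165.9, and rounding up per site gives 171.

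**Step 3: does shared centre variation cost power?** Simulation used individual allocation in nine sites with balanced arms, a gamma-distributed site rate common to both arms, Poisson counts and 20,000 replicates:

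| Per arm | CV 0.01 | CV 0.10 | CV 0.30 |
|---|---|---|---|
| 124 | 80.1% | 80.2% | 79.6% |
| 171 | 91.3% | 91.0% | 90.9% |

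The loss is negligible.

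**Step 4: power on the plan's own inputs.** On the log scale, with |ln 0.70| = 0.3567 and 1/1.20 + 1/0.84 = 2.0238, power at 171 is Φ(0.3567/√(2.0238/171) − 1.96) = Φ(1.32) = 0.906. The rate-difference form gives 0.909. After 15%-20% loss, 200 per arm leaves 170-160, where power is 0.905-0.887.

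**Step 5: secondary outcomes.** The detectable difference with 171 per arm is 2.802 × SD × √(2/171) = 0.303 × SD.

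| Outcome | SD | Recomputed | Stated | Implied variance inflation |
|---|---|---|---|---|
| BBS | 6.15 | 1.9 | 3.0 | 2.6 |
| BESTest | 13 | 3.9 | 6.4 | 2.6 |
| ABC | 23.2 | 7.0 | 11.5 | 2.7 |
| Chair stand | 4.8 | 1.5 | 2.4 | 2.7 |

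**Step 6: what the size tolerates under the planned model.** With negative binomial dispersion d, the variance becomes (2.0238 + 2d)/n. Setting power to 80% gives d = (n × 0.1272/7.849 − 2.0238)/2, which is 0.28 at n = 160 and 0.37 at n = 170. The documents give no dispersion value. For assumed values, power at 160-170 per arm is:

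| Assumed d | Power |
|---|---|
| 0.25 | 81%-83% |
| 0.5 | 74%-76% |
| 1.0 | 61%-64% |

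**The case against.** The strongest reply is that the formula's k² term adds independent variation to each arm within each site. In a within-site trial that is equivalent to variation of the treatment effect between sites, with an SD of the log rate ratio of about √2 × 0.10 = 0.14. Adding 0.14²/9 to the variance gives about 85% power at 171 per arm and about 75% at 124 (normal approximation). Such variation is plausible: rehabilitation lasts 8-12 weeks depending on site, there are four countries, and the supervised balance sessions may be worked through in groups. This part stands. It would be too strong to infer that the extra 47 per arm serve no purpose, or that no form of clustering could matter. But the section gives clustering of participants within centres as its reason and mentions neither effect variation nor group delivery.

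Two further points are fair. The cited method is not available, so the formula is identified by the exact match and the type of input, not by name. And the step is conservative under Poisson counts, so it does not by itself make the trial too small.

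**Conclusion.** Wrong as written. The arithmetic is correct, but the method does not fit the design. On the plan's own inputs the stated 80% at 171 per arm is about 91%, or about 89-90% at the expected evaluable number, and the four secondary detectable differences are overstated by a factor of about 1.6.

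This rests on two-sided testing, the normal approximation, a centre effect common to both arms, one full year of follow-up for those evaluable, and no data from those lost.

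Two stronger readings are not supported. A reader might infer that the trial is oversized and could be cut; but 91% holds only for pure Poisson counts, and the planned model allows for overdispersion, under which power may fall below 80%. A reader might also take 0.28-0.37 as a dispersion that the sponsor expects. It is solved back from the sample size and shows only what that size tolerates.

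**What to change.** Keep 400 participants and revise the Sample Size Calculation section:

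- Remove the cluster-trial justification. State that randomisation is individual and stratified by site, with centre in the model.
- Restate power at the expected 160-170 evaluable per arm over a range of negative binomial dispersion values. Note that 80% holds up to about 0.28-0.37, as a tolerance and not as a prior assumption.
- If an allowance for variation of the treatment effect between sites is intended, say so and give its value.
- Recompute the four secondary detectable differences on the same basis.

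The cost is a rewritten section and a short recalculation; recruitment and conduct do not change. The downside is that the new power statement may look less favourable if dispersion is high.

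### The detectable differences for the four secondary outcomes do not follow from 171 per arm with a clustering effect similar to the primary outcome's; they are 37-41% too large on the plan's own inflation

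*Protocol article*

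**What the plan says.** The Sample Size Calculation section first sizes the trial on falls: "the estimated number of participants in each arm with 1-year follow up is 124 patients". It then allows for the nine centres: "Assuming a coefficient of variation of size 0.10, we need, on average, 19 participants in each arm per site", which gives 171 per arm.

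The premise for the secondary outcomes is "Assuming a similar clustering effect for the secondary outcomes with a sample size of 171 participants in each arm and nine centers". On that basis the section makes its claim about sensitivity, namely that "our study has 80% power with 5% type I error to detect differences of the following magnitudes". The first entry in its list is "Berg Balance (SD=6.15, MCID=5) differences of 3.0 units or larger"; the other three are BESTest 6.4 (SD 13), ABC 11.5 (SD 23.2) and chair stand 2.4 (SD 4.8). The section sums up: "These values are close to half the standard deviation of the outcome measures". No intraclass correlation (ICC), design effect or outcome mean is given for any secondary outcome.

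**The concern.** A two-arm comparison with 171 per arm normally has 80% power for about 0.3 SD, so half an SD looks large. Reaching it takes far more inflation for clustering than the primary outcome received, yet the text calls the clustering effect similar.

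The stated sensitivity of every balance, balance-confidence and strength outcome is at stake. A reader would conclude that effects below half an SD are out of the trial's reach, when on the plan's own inputs it can detect about 0.36 SD or less.

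**Working it through.** **Inputs** (Sample Size Calculation): 80% power; 5% type I error, taken as two-sided because sidedness is not stated; fall rates 1.20 and 0.84 per person-year; coefficient of variation k = 0.10; nine centres; 171 per arm; the four SDs. From the Allocation section: each site has its own randomisation schedule, and individuals are allocated. Z = 1.960 + 0.842 = 2.802, and Z² = 7.849.

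**Step 1: the primary figures reproduce.**
- Unclustered: n = Z²(r0 + r1)/(r0 − r1)² = 7.849 × 2.04/0.1296 = 123.5, so 124 per arm.
- Clustered, with the cluster-trial formula for rates: c = 1 + Z²[(r0 + r1)/y + k²(r0² + r1²)]/(r0 − r1)². With y = 18 per site and arm, c = 9.16; with y = 19, c = 8.80. Nine centres therefore need 19 per site and arm (solving for y gives 18.4), and 9 × 19 = 171.
- The inflation shown is 171/124 = 1.379.

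**Step 2: the secondary figures.** For two means, the detectable difference is Z × SD × √(2 × DE/n), with n = 171 and DE the design effect.
- DE = 1.379: 2.802 × √(2 × 1.379/171) = 0.356 SD.
- DE = 1: 2.802 × √(2/171) = 0.303 SD.

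| Outcome | SD | Stated (in SD) | DE 1.379 | Stated excess | DE 1 | Stated excess |
|---|---|---|---|---|---|---|
| Berg | 6.15 | 3.0 (0.488) | 2.19 | 37% | 1.86 | 61% |
| BESTest | 13 | 6.4 (0.492) | 4.63 | 38% | 3.94 | 62% |
| ABC | 23.2 | 11.5 (0.496) | 8.25 | 39% | 7.03 | 64% |
| Chair stand | 4.8 | 2.4 (0.500) | 1.71 | 41% | 1.45 | 65% |

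Power at the stated differences is 97.0-97.6% with DE 1.379 and 99.5-99.6% with DE 1.

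**Step 3: what the stated figures imply.** Solving for DE at n = 171, DE = (difference/SD)² × 171/(2Z²), which gives 2.59 (Berg), 2.64 (BESTest), 2.68 (ABC) and 2.72 (chair stand). That is about twice 1.38. With 19 per site and arm it corresponds to an ICC of about 0.09, since (2.64 − 1)/18 = 0.091.

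**Step 4: a possible source.** Rounding does not explain the gap, because one SD multiple between 0.4935 and 0.4959 fits all four figures. Using 0.10 as an ICC with 200 per arm in nine clusters gives DE = 1 + (200/9 − 1) × 0.10 = 3.12 and 2.802 × √(2 × 3.12/200) = 0.495 SD. The differences are then 3.04, 6.44, 11.48 and 2.38, which round to all four stated values. The same ICC with 171 per arm gives DE 2.8 and 0.507 SD (3.12, 6.59, 11.76, 2.43), which does not match.

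**Step 5: other variants at 171 per arm.** One-sided 5% with DE 1.379 gives 0.316 SD; 90% power with DE 1.379 gives 0.412 SD; a type I error of 0.05/4 with DE 1.379 gives 0.424 SD. None reaches the stated set.

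**The case against.** Four points can be made for the plan.

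1. **The figures are not arbitrary.** Step 4 reproduces all four from 0.10 and 200, both of which appear in the section. This probably explains them, but it is an inference. The article ties the figures to 171 rather than 200, and presents 0.10 as a coefficient of variation, which is not an ICC. The design effect used is also that of a cluster-randomised trial, whereas here individuals are randomised within site. The source would explain the error without curing it.

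2. **A similar clustering effect need not mean a ratio of 1.38.** It could mean k = 0.10 carried into the cluster formula for means. That result depends on outcome means, which the article does not give. For assumed Berg means of 40 to 50 the detectable difference would be 5.9 to 7.3, and for assumed BESTest means of 60 to 80 it would be 9.4 to 12.0. The stated set would require means of about 16 (Berg) and 35 (BESTest). So this reading does not yield the stated figures either, but under it the stated Berg and BESTest values would be too small. The direction of the error is therefore established only for the 1.00 to 1.38 readings.

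3. **Zero clustering is not the plan's premise.** This stands. Centre main effects largely cancel when individuals are randomised within site, but treatment-by-centre variation does not, and the training is supervised at each site. A reader might conclude that the figures are simply about 60% too large with true power of 99.5%. Those sizes hold only against the no-clustering benchmark. On the article's own inflation they are 37-41% and about 97%.

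4. **Little depends on it.** This also stands. Every stated difference is below its MCID (3.0 < 5, 6.4 < 13, 11.5 < 19, 2.4 < 3), so the claim that clinically important changes are detectable survives. The target of 400 comes from the falls calculation, which reproduces. A reader might infer that the trial is wrongly sized; the document does not support that.

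**Conclusion.** The point holds as an internal inconsistency: the stated power, sample size, SDs and clustering premise do not produce the four stated differences. If the primary outcome's 1.38 is taken as the similar effect, the correct figure is about 0.36 SD. With individual randomisation within site and no residual clustering, it is about 0.30 SD. Both assume two-sided 5%, a normal approximation, the article's SDs without baseline adjustment, and 171 evaluable per arm. On these readings the trial's sensitivity is understated, so the error is conservative. It is worth correcting because it misstates the precision of all four secondary outcomes, but it changes neither the sample size nor the design.

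**What to change.** Restate the four differences for 171 evaluable per arm, and name the design effect behind them:
- about 0.30 SD for individual randomisation within site (Berg 1.9, BESTest 3.9, ABC 7.0, chair stand 1.5); or
- about 0.36 SD as a conservative figure, using the article's inflation of 1.38 (2.2, 4.6, 8.3, 1.7).

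Change the sentence that describes the values as about half an SD to match. If the authors did use an ICC of 0.10 or 200 per arm, they should say so and explain why a cluster-trial inflation applies when individuals are randomised within site. The cost is wording only: no change to recruitment, data collection or analysis.

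### The planned 400 participants do not retain the required 171 per arm at the anticipated 15%-20% loss; the effect on power is small and confined to the upper part of that range

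*Protocol article*

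**What the plan says.** Everything needed is in the Sample Size Calculation section of the protocol article.

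- The starting point is an individually randomized comparison with 80% power and 5% type I error. The control rate is 120 falls per 100 person-years and the intervention rate is 84, a 30% reduction. From this, "the estimated number of participants in each arm with 1-year follow up is 124 patients".
- The number is then raised because participants are recruited in nine centers. With a coefficient of variation of 0.10, the article arrives at an average of 19 per arm in every center. Over the nine this becomes the requirement, "corresponding to a total of 171 participants in each arm, to account for the clustering of the study".
- The same 171 per arm is the basis for the detectable differences quoted for the four secondary outcomes.
- Last comes the allowance for attrition: "We anticipate a loss to follow-up of 15%-20% based on previous trials in PR and have inflated our sample size to 400 participants", given as 200 in each arm.

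**The concern.** The article gives a required number, an expected loss and an enrolment target, and says that the third follows from the first two. It does not. If 171 per arm must remain after losses, 200 per arm is too few at both ends of the stated range and everywhere between. The 171 has to be read as a number with complete follow-up: the 124 from which it grows is for one year of follow-up, and the loss allowance is applied after it.

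At stake is whether the declared 80% power for the primary outcome, and the detectable differences stated for the secondary outcomes, still hold at the loss the investigators themselves expect.

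**Working it through.** **Inputs (all from Sample Size Calculation).** Control rate λ0 = 1.20 and intervention rate λ1 = 0.84 per person-year; power 80%; type I error 5% (taken as two-sided, which reproduces the article's figure; one-sided gives 98); c = 9 centers; coefficient of variation k = 0.10; required 171 per arm; loss 15%-20%; enrolment 200 per arm.

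**Step 1. Reproduce 124.** With (1.960 + 0.842)² = 7.849,

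n = 7.849 × (λ0 + λ1)/(λ0 − λ1)² = 7.849 × 2.04/0.1296 = 123.5, so 124. This agrees.

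**Step 2. Reproduce 171.** The article cites a source for the clustering step but does not print the formula. The standard formula for comparing rates between clusters, with y person-years per arm per center, is

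c = 1 + 7.849 × [(λ0 + λ1)/y + k²(λ0² + λ1²)]/(λ0 − λ1)².

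Here k²(λ0² + λ1²) = 0.01 × (1.44 + 0.7056) = 0.021456. Solving at c = 9:

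y = 2.04/(8 × 0.1296/7.849 − 0.021456) = 18.44.

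Rounded up this is 19 per site, and 19 × 9 = 171. This agrees. The unrounded requirement is 18.44 × 9 = 165.9 per arm.

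**Step 3. Apply the loss.**

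| Loss | Remaining of 200 | Enrolment per arm to keep 171 | Total |
|---|---|---|---|
| 14.5% | 171 | 200 | 400 |
| 15% | 170 | 171/0.85 = 201.2, so 202 | 404 |
| 17.5% | 165 | 171/0.825 = 207.3, so 208 | 416 |
| 20% | 160 | 171/0.80 = 213.75, so 214 | 428 |

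The largest loss that leaves 171 is 1 − 171/200 = 14.5%. Against the unrounded 165.9 it is 1 − 165.9/200 = 17%.

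**Step 4. Power for falls by the formula of step 2**, if lost participants contribute nothing:

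power = Φ( √{8 × 0.1296/[2.04/y + 0.021456]} − 1.96 ), with y = n/9.

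- n = 171: 81.0%
- n = 170: 80.8%
- n = 166: 80.0%
- n = 165: 79.8%
- n = 160: y = 17.78, √(1.0368/0.1362) − 1.96 = 0.799, so 78.8%

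**Step 5. Partial follow-up.** The formula counts person-years, so time observed before loss can be added. The article does not say how long lost participants are observed, so this is an assumption with a range. At 20% loss, 40 per arm are lost. If they contribute nothing, power is 78.8%. If they contribute half a year on average, 160 + 20 = 180 person-years remain and power is 82.6% (at 15% loss: 185 person-years, 83.4%). To regain the unrounded 165.9 they need to contribute 5.9/40 = 0.15 year each on average, a little under two months.

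**Step 6. Secondary outcomes.** Detectable differences scale roughly with 1/√n: √(171/160) = 1.034.

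| Measure | At 171 per arm | At 160 per arm | Stated MCID |
|---|---|---|---|
| Berg Balance | 3.0 | 3.1 | 5 |
| BESTest | 6.4 | 6.6 | 13 |
| ABC | 11.5 | 11.9 | 19 |
| Chair stand | 2.4 | 2.5 | 3 |

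**The case against.** The best defence concedes the head count and disputes that it matters. Three of its arguments deserve weight.

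1. **Rounding.** At 15% loss the gap is one participant per arm and power is still 80.8%. Because 171 was rounded up from about 166, the power target is met to about 17% loss. This stands: the lower part of the range is safe for power, though not for the stated 171.

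2. **Person-time.** Falls come from monthly diaries, and participants who do not return them are telephoned (Primary Outcome). Assessments are to be attempted after withdrawal (Retention) and may be done at home. A participant lost late may already have supplied most of a year of data. This stands for the primary outcome, subject to the analysis using partial follow-up, which the article does not say. It does not help the balance, confidence and strength measures at 12 months, because a missed visit yields no value.

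3. **Clustering.** Individuals are randomized with a schedule for each site, and the model adjusts for center, so the step from 124 to 171 may be generous. With the unclustered formula of step 1, 160 per arm gives √(160 × 0.1296/2.04) − 1.96 = 1.23, or about 89% power. This is a fair reason not to be alarmed. But the article presents 171 as the requirement and not as a cushion, and the attrition statement has to be judged against it.

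A reader might also infer that the investigators multiplied 171 by one plus the loss instead of dividing by one minus the loss. The article does not give its method. Multiplication gives 197 at 15% and 206 at 20%, and rounding 201.2 down to 200 would explain the target equally well. The cause is unknown and the point does not need it.

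**Conclusion.** The sentence is wrong as written: 200 per arm does not retain 171 at any loss between 15% and 20%. The shortfall runs from 1 to 11 per arm, and nothing else in the article corrects it.

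The size of the effect is small. By the formula that reproduces the article's own figures, 80% power holds to about 17% loss and is 78.8% at 20%, which is 1.2 points under target. That figure assumes Poisson counts, the stated clustering allowance, and no fall data from lost participants. With partial diary data the primary-outcome shortfall shrinks or disappears. The secondary detectable differences grow by about 3%, and all stay below the stated MCIDs, so the article's conclusion about them survives.

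A reader might infer that the trial is underpowered across the whole anticipated range. The documents do not support that: the whole-range failure concerns the head count of 171, not the power. Nor can the shortfall be enlarged by assuming overdispersed counts. A negative binomial model is named in Data Analysis, but the article gives no dispersion value, and that would be a separate question from attrition.

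**What to change.** Keep 400. Replace the claim that it accounts for 15%-20% loss with a statement that 200 per arm retains 171 up to 14.5% loss and, by the formula used, 80% power up to about 17%. Add the power at 20% loss (about 79% if lost participants contribute no fall data) and the secondary detectable differences for 160 to 170 per arm.

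This costs a sentence or two and a slightly less favourable stated power at the upper end of the loss range. No extra recruitment is needed. The alternative, enrolling 428 to cover the whole range, would add 28 participants for a gain of about two points of power at 20% loss (78.8% to 81.0%).
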